### 8.9 Data Collection and Statistical Analysis

Data about individual participant will be collected by the study team using structured questionnaires and coded, de-identified labels which will be held in strict confidence. All results will be presented in a way that does not allow individuals to be identified. No information concerning the study or the data will be released to any unauthorized third party. These questionnaires are presented in the appendix of this protocol. The study team will rely on electronic data capture and will convert these forms to the ODK electronic format at the London School of Hygiene and Tropical Medicine.

Table 4: Data Collection Summary for AE reporting

| Forms                                                                                  | Timeline                                                                                                           | Person responsible for filling out the form |
|----------------------------------------------------------------------------------------|--------------------------------------------------------------------------------------------------------------------|---------------------------------------------|
| Informed Consent                                                                       | Pre-MDA Census days and Distribution Day                                                                           | HEW/Clinical Nurses                         |
| Socio-demographic/health Information                                                   | Distribution Day                                                                                                   | Clinical Nurses                             |
| Study drug registry                                                                    | Distribution Day                                                                                                   | Clinical Nurses                             |
| Contra-indication/AEs reporting to the Co-Administration team (HEW and clinical nurse) | Day 2, Day 4, Day 6, Day 8, Day 10, Day 12, Day 14, Day 17+18 follow up or at any time during passive surveillance | Clinical Nurses/HEW                         |
| Contra-indication/AEs reporting to the local health post (HEW)                         | Day 19-30                                                                                                          | HEW                                         |

\* Study team will return to each health post at 1 month after the MDA to collect information on reported AE/SAEs

Data will be entered in STATA. All variables will be summarized using descriptive statistics as is appropriate. The co-administration safety will be characterized as safe or unsafe.

Parameters to be determined are:

- Population of study kebeles: composition by age group and sex.
- Prevalence and incidence of adverse events by age group, sex, and kebele
- Severity of adverse events in each kebele
- Average age of participant experiencing adverse events

The null hypothesis is that the occurrence of adverse events will be significantly higher in the co-administration trial communities in comparison to the standard MDA control communities. The study will report the proportion of individuals in each arm experiencing an AE adjusting for

clustering. It will also report the proportion of AEs stratified by age group. The test statistic will be clustered logistic regression using the covariates of severity and treatment package.

It is important to note that we consider that if the number of adverse events in the co-administration arm was markedly higher than in separate administration arms, for example >5% absolute difference in AEs, then the increased number of adverse events would likely outweigh any logistic or cost benefits. However, a stricter non-inferiority margin of 1.5% was used as the basis for the sample size calculation and was selected for two reasons:

- 1) If the trial results in non-inferiority at this level the study believes this represents unequivocal evidence in favour of co-administration; i.e given the absence of a marked increase in adverse events, the logistic and financial advantages mean the rationale in favour of co-administration is clear.
- 2) To provide a more precise estimate of the difference in the proportion of adverse events in the control and intervention arms.

If the trial were not to meet this non-inferiority margin (i.e the upper limit of the 95% CI crossed our specified delta of 1.5%) but did not cross the threshold at which the increase in the number of AEs was clearly unacceptable (5% difference) then the study believes that plausibly co-administration might still be favourable even accepting that it did result in more adverse events were the logistic and financial benefits to be marked.

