Within our standard arm, the study will deduce the average adverse event rate for azithromycin administered alone using information from previous trials, and it will assume an average adverse event rate for azithromycin, ivermectin and albendazole administered together. For azithromycin, there is a wide-range of reported adverse event rates. The aforementioned co-administration trial in Mali assumed an adverse event rate of 8%. A randomized control trial using a single dose of azithromycin which took place in the United States reported adverse events at 17%. A randomized control trial in Ethiopia reported that monitored adverse event rates after Zithromax MDA reported 4.9%-7.0% adverse events in children from 1-9 years old and 17.0% to 18.7% in persons  $\geq 10$  years of age. Meanwhile, Pfizer labeling reports the following: "Side effects that occurred in patients on the single one-gram dosing regimen of Zithromax with a frequency of 1% or greater included diarrhea/loose stools (7%), nausea (5%), abdominal pain (5%), vomiting (2%), dyspepsia (1%) and vaginitis (1%)." For the purposes of this study, we will set the adverse event percentage at 7% for azithromycin distribution. In terms of the adverse even rate during co-administration of all three drugs, adverse events related to IVM and ALB distribution are largely due to the death of microfilariae, particularly after the first round of MDA in a community. Given that this community has received several years of treatment with both drugs, we assume an acceptable increase in adverse events during co-administration will be 1.5% (Delta), or it will be acceptable for 8.5% of our intervention arm to experience an adverse event.

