The study will require a power of 90% and a two-sided 95% confidence interval for the difference between rates. Given that gotes will be randomly selected from within the same woreda, have all had the same number of years of treatment with each drug, and share the same cultural and environmental factors, we will assume a low variability between each cluster. In case there are unforeseen differences between the clusters, we will include a variance between 6-8%. Conservatively assuming that each gote has a population of 190 individuals, the study will require at least 36 gotes in each study arm to reach 13,600. To take non-compliance, etc. into account, the study will randomize the 42 gotes into each study arm to reach 8,000 participants in each arm from the list of gotes in Kofele woreda into the control and study arms until each arm has 8,000 participants (to account for non-compliance, etc.). Gotes will be chosen via the RANDNUM function in excel. The randomization itself will be conducted via public randomization ceremonies.

Table 2: Assumption Summary

|                                                               |                                                           |
|---------------------------------------------------------------|-----------------------------------------------------------|
| Adverse event prevalence                                      | 7% on average                                             |
| Acceptable adverse event percentage during co-administration: | 8.5%                                                      |
| Delta                                                         | 1.5%                                                      |
| Variance                                                      | Adverse event prevalence between clusters will be 6-8%    |
| Power                                                         | 90%                                                       |
| CI                                                            | 95%                                                       |
| Minimal Number of Gotes Required for each arm                 | 36                                                        |
| Population per cluster                                        | 190 individuals per cluster (gote) on average             |
| Total Population of Study                                     | 13,600 (Rounded to 16,000 for refusals/loss to follow up) |

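### Section 8.9 states a null without a margin and an odds-ratio test, which contradict the protocol's own 1.5-point confidence-interval rule

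*Protocol*

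**What the plan says.** Section 8.1 chooses a non-inferiority design, sets Delta at 1.5 points (7% to 8.5%) and calls for "a two-sided 95% confidence interval for the difference between rates". Section 8.9 confirms that "a stricter non-inferiority margin of 1.5% was used as the basis for the sample size calculation", and says the margin is not met if "the upper limit of the 95% CI crossed our specified delta of 1.5" per cent. It adds a second, looser threshold: ">5% absolute difference in AEs, then the increased number of adverse events would likely outweigh any logistic or cost benefits".

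Earlier in section 8.9 the formal test, which sets this arm against the controls, is described differently: "The null hypothesis is that the occurrence of adverse events will be significantly higher in the co-administration trial communities". The statistic follows a little later: "The test statistic will be clustered logistic regression using the covariates of severity and treatment package". Neither sentence mentions 1.5 points or a difference in rates.

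Wording without a margin also appears where the result is used. The Study Protocol Summary makes triple therapy for the rest of the district depend on there being no increase in AEs. Section 8.5 and the DSMB charter (Appendix 10) have the board convened if mild or moderate AE rates differ significantly between arms, including at Day 31, when treatment of the remaining population is decided.

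**The concern.** A non-inferiority null is a statement about a parameter: the true excess is at least 1.5 points. A null that AEs are significantly higher has no margin and describes the outcome of a test. Taken at its word, it is overturned by any non-significant comparison, so imprecision works in favour of the new regimen. The named test points the same way, because the usual output of a logistic model is an odds ratio compared with 1.

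The decision rule a few lines later asks something else. The protocol therefore offers two criteria for its primary safety conclusion without saying which governs. One is weaker than the other in exactly the situation the trial is meant to guard against, a modest real increase in AEs.

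**Working it through.** **Inputs.** Control rate 7%, margin 1.5 points, 90% power, two-sided 95% CI, 190 people per gote, at least 36 gotes per arm with 42 to be randomised (section 8.1). Cluster AE rates of 6-8% (Table 2) are read as mean plus or minus 2 SD, so SD = 0.5 points and CV k = 0.005/0.07 = 0.0714. That reading is an assumption.

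**1. The plan's own figure.** Cluster formula on the risk difference, true rates equal:

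c = 1 + (1.96 + 1.2816)² × [2p(1−p)/m + 2k²p²] / margin²

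= 1 + 10.508 × [0.000685 + 0.000050] / 0.000225 = 35.34, rounded up to 36 gotes, or 6,840 per arm.

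This matches the protocol, so the stated size fits a 1.5-point margin on the difference scale. With SE 0.45 points under equal rates, power is 91% at 36 gotes and 95% at 42.

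**2. Where the two criteria disagree.** SE² = {[p₀(1−p₀) + p₁(1−p₁)]/m + k²(p₀² + p₁²)}/c.

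At 7% vs 7.75% with c = 36: [0.000719 + 0.0000556]/36, so SE = 0.46 points and 1.96 × SE = 0.91 points.
- Non-inferior if the observed difference is below 1.5 − 0.91 = 0.59 points.
- Significantly higher if it is above 0.91 points.
- From 0.59 to 0.91 points the result is not significantly higher, yet misses the margin.

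Example, 7.0% vs 7.8%: difference 0.8 points (CI −0.1 to 1.7); odds ratio 1.12 (0.98 to 1.28), p = 0.085.

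**3. Chance of accepting a true excess of 1.5 points.** The margin rule accepts 2.5% of the time. The margin-free reading accepts with probability Φ(1.96 − 0.015/SE).

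| Control rate | Gotes per arm | SE (points) | Margin-free acceptance |
|---|---|---|---|
| 7% | 36 | 0.475 | Φ(1.96 − 3.155) = 11.6% |
| 7% | 42 | 0.440 | Φ(1.96 − 3.408) = 7.4% |
| 15.8% | 36 | 0.694 | Φ(1.96 − 2.162) = 42% |

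The 15.8% is the standard-arm rate of the Mali trial in section 4, with the same k; it is a sensitivity value, not this plan's assumption. At 7% and 36 gotes, no clustering (k = 0, SE 0.457) gives 9.3%. Reading 6-8% as plus or minus 1 SD (k = 0.143, SE = √{[0.000752 + 0.000247]/36} = 0.527) gives Φ(1.96 − 2.847) = 18.8%.

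**4. An odds ratio cannot stand in for the margin.** An excess of 1.5 points is (0.085/0.915)/(0.07/0.93) = 1.234 at a 7% control rate, but (0.173/0.827)/(0.158/0.842) = 1.115 at 15.8%. A fixed limit of 1.234 would allow 3.0 points at 15.8%.

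**5. The opposite conflict.** To be significantly higher and inside the margin, the whole CI must lie between 0 and 1.5 points, so its width must be under 1.5. At a 7% control rate the width is 2 × 0.91 = 1.8 points with 36 gotes and 1.7 with 42, so this cannot occur. It can at lower rates: 2.6% vs 3.35% (2.6% being the overall AE rate of the Solomon Islands study in section 4) has SE 0.295 and CI 0.2 to 1.3 points.

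**The case against.** The strongest reply is that the non-inferiority test is in the protocol. Section 8.1 fixes the margin and the interval, section 8.9 says when the margin is missed, and the sample size reproduces on that basis. Nothing says outright that a non-significant result establishes non-inferiority. On this view the null sentence is loose wording that a sensible analyst would override.

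Much of that stands. A reader might infer that the 1.5-point claim is never tested; the documents do not support this, because the interval rule is explicit. A reader might also infer that logistic regression is the wrong model. It is not: marginal standardisation turns a clustered logistic fit into a risk difference with a CI. That the protocol does not name the step producing the interval is detail that may sit in an analysis plan not shown here, and is no fault. Nor do the two criteria conflict in both directions at a 7% control rate (step 5).

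What does not stand is that the matter is only deferred detail. The protocol itself states the null, the test and the decision rule, and they disagree. An analysis plan that copied the null and test would inherit the contradiction, and the margin-free wording recurs in the Summary, section 8.5 and the DSMB charter.

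**Conclusion.** The point holds as an internal contradiction: the null and test in section 8.9 do not correspond to the rule in sections 8.1 and 8.9 that the upper limit of the CI for the difference must stay below 1.5 points. Under the plan's assumptions the practical risk is false reassurance. At a true excess equal to the margin, the margin-free reading accepts about 12% of the time with 36 gotes or 7% with 42, instead of 2.5%. It would reach 42% with 36 gotes if the control rate were 15.8%. The exact figures depend on how the 6-8% range is read (9% to 19% at 36 gotes across the readings shown); the contradiction does not. The design and sample size are not in question.

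**What to change.** In section 8.9, replace the null and test sentences so that they:

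- state H0: pT − pC ≥ 1.5 points against H1: pT − pC < 1.5 points, where pT and pC are the proportions with an AE under co-administration and standard MDA;
- make the cluster-adjusted risk difference with a two-sided 95% CI the primary estimate (marginal standardisation of the logistic model is acceptable);
- declare non-inferiority only if the upper limit is below 1.5 points, with no other criterion for that claim;
- report the odds ratio as supportive.

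The Summary, section 8.5 and Appendix 10 should then be reconciled with this rule wherever they describe the end-of-study comparison. The cost is a few sentences. Sample size, margin and data collection stay as they are.

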## 4. Feasibility of Triple Drug Co-Administration Based on Existing Data

### 4.1. Pharmacokinetic Data on Combined Drug Interaction of azithromycin, ivermectin and albendazole

Pharmacokinetic studies have demonstrated that there is little to no drug-to-drug interaction between ivermectin and albendazole. Mass co-administration of both drugs to treat LF has also occurred with no reported serious adverse events related to drug to drug interactions among large populations for many years. The question lies in the safety of adding azithromycin to the albendazole/ivermectin combination. In a randomized, three-way crossover pharmacokinetic study on the interaction between azithromycin, ivermectin and albendazole, 18 volunteers were administered 500 mg of azithromycin, 400 mg of albendazole, and a dose proportional to body weight of ivermectin concurrently. The results of the study found the interactions between albendazole and azithromycin to be small enough to be of little clinical importance. The total drug exposure over time for ivermectin increased by 31% among the volunteers. This trend of higher peak blood levels of ivermectin when co-administered with azithromycin has been demonstrated within pharmacokinetic models to be well within safety ranges. The study author goes on to say in conclusion that the population pharmacokinetic model analyses “support further study of co-administration of azithromycin with the widely used agents ivermectin and albendazole, under field conditions”.

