### 8.4 Recording of any AE/SAEs

The study defines AEs and SAEs per the national guidelines which are also found in the Serious Adverse Events handbook created by RTI ENVISION and the Task Force for Global Health:

**“Adverse event from MDA (AE-F-MDA)** is a medical event that takes place in an MDA program, causes concern in the medical and wider community and is believed to be caused by the drug(s) used. It can be caused by either administration of the drug or by a coincidental event that by chance happened after drug administration. Most AEs-f-MDA (adverse events from MDA) are self-limiting and treatable using simple remedies and are not usually required to be reported to national or international regulatory authorities.

**Serious Adverse Event (SAE)** is a regulatory term describing any untoward medical occurrence with any of the following characteristics:

- Results in death;
- Requires in-patient hospitalization;
- Results in persistent or significant disability;
- Is life-threatening; or
- Results in a congenital anomaly/birth defect.”

All adverse events will be recorded and followed up by the nurses on the team. The reporting of adverse events will be systematic and comply with national AE/SAE reporting guidelines to avoid any bias related to the wording of the question(s).

While the difference between “adverse events” and “serious adverse events” have been described above, there is also a level of severity which the study will also monitor: “The term “severe” is often used to describe the intensity (severity) of a medical event, as in the grading “mild”, “moderate”, and “severe”; thus a severe action need not be serious.” Reported adverse events will be classified according to their intensity (none, mild, moderate, and severe).

- Mild: easily tolerated, does not interfere with daily activity,

- Moderate: uncomfortable enough to interfere with daily activity,
- Severe: precludes daily activity (Given that a “severe” adverse event includes inability to complete daily activities, it will be classified as a possible SAE for the purposes of this study.)

The evolution of older complaints will be classified as: exacerbated, ongoing, and improved or resolved/none.

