## 10 Timetable for Study Completion

[figure not shown]

The Primary outcome is

- The safety as can be measured by incidence of AEs/SAEs over one month following the co-administered MDA in comparison to a control group receiving the standard MDA regimen.

Secondary Outcomes are:

- Understanding the perceptions of the beneficiaries receiving the co-administration of azithromycin, ivermectin, and albendazole especially surrounding pill burden and the change in MDA distribution schedule.
- Understanding the perceptions of the co-administration strategy by the local health workforce as a means of PC-NTD drug delivery.
- A cost analysis comparing existing MDA unit costs from woredas within the region already on a standard MDA schedule with that of the co-administered woredas.

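### The stated non-inferiority rule counts adverse events of any grade, and no section sets out a comparison of severe events between the arms

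*Protocol*

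**What the plan says.** **Outcome and rule.** Section 10 of the protocol gives the primary outcome as "The safety as can be measured by incidence of AEs/SAEs over one month following the co-administered MDA", compared with the control group. Section 8.9 says "The co-administration safety will be characterized as safe or unsafe" and reduces the outcome to one quantity: "The study will report the proportion of individuals in each arm experiencing an AE", adjusted for clustering. Non-inferiority fails if "the upper limit of the 95% CI crossed our specified delta of 1.5" per cent. Success on this rule is described as unequivocal support for co-administration. The looser threshold uses the same count: "for example >5% absolute difference in AEs". Neither threshold has a severity condition.

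**Severity.**
- Section 8.4 grades every AE. Mild events are easily tolerated. The next grade is defined as "Moderate: uncomfortable enough to interfere with daily activity". Severe events prevent daily activity.
- Section 8.9 lists "Severity of adverse events in each kebele" among the parameters, and names severity beside treatment package as a covariate in the clustered logistic regression.
- Section 8.5 and the DSMB charter (Appendix 10) trigger a call if the rate of mild/moderate events differs significantly between arms. They treat any severe AE as a possible SAE, which triggers a call in its own right.
- Section 8.5 analyses severe AEs and SAEs at three levels of pre-existence and causality. It names no comparison between arms.

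**The concern.** In a trial whose primary outcome is safety, the formal verdict gives an easily tolerated event the same weight as one that prevents daily activity. If triple therapy left the number of affected people unchanged but made their events worse, the 1.5-point rule would not register it.

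The other stated analyses do not fill the gap. A table by kebele is not a table by arm, and gotes, not kebeles, are what section 8.1 allocates. Severity exists only once an AE has occurred, so it cannot serve as an adjusting covariate for AE yes/no and gives no test of severe events by arm. The DSMB's one stated test between arms leaves out the severe grade.

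Intensity is a fair question here, because section 4.1 reports of the pharmacokinetic study that "The total drug exposure over time for ivermectin increased by 31% among the volunteers".

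At stake is whether the plan's strongest favourable conclusion can be drawn before anyone has set the rates of severe events in the two arms side by side.

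**Working it through.** **1. Reproduce the sample size, to confirm which endpoint it serves.** Inputs from section 8.1 and its Table 2: AE rate p = 7%, margin 1.5 points, 90% power, two-sided 95% interval, m = 190 per gote, gote prevalence 6–8%. I read that range as ±2 SD, so SD = 0.5 point and k = 0.005/0.07 = 0.071. This reading is an assumption.

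c = 1 + (1.96 + 1.2816)² × [2p(1−p)/m + 2k²p²] / 0.015²
= 1 + 10.508 × (0.000685 + 0.000050) / 0.000225
= 35.34, rounded up to 36 gotes per arm.

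This matches the protocol (36 × 190 = 6,840 per arm; 13,680 in total). The trial is sized on AEs of any grade.

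**2. Chance of declaring non-inferiority when any-AE is 7% in both arms.**

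SE = √{2 × [0.07 × 0.93/6,840 + 0.005²/36]} = 0.00452

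With an observed difference of zero, the upper limit is 1.96 × 0.00452 = 0.89 point.

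Probability = Φ(0.015/0.00452 − 1.96) = Φ(1.36) = 91%.

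With 42 gotes per arm it is 95%. With 36 gotes and an SD of 1 point it is 86%. Severity does not enter the formula, so the result is the same for any grade mix.

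**3. What can change behind the same verdict.** The protocol gives no severe rate. Assume that 5% of AEs are severe in the control arm. About 6,840 × 0.07 = 479 people per arm have an AE.

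| Severe share of AEs, triple arm | Severe cases, control vs triple | Severe difference (unadjusted 95% CI) | Any-AE difference |
|---|---|---|---|
| 5% | 24 vs 24 | 0 (−0.20 to 0.20) | 0 |
| 25% | 24 vs 120 | 1.40 points (1.06 to 1.74) | 0 |
| 50% | 24 vs 239 | 3.15 points (2.69 to 3.61) | 0 |

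**4. What a by-arm comparison would add.** With q₀ and q₁ the control and triple-arm rates, and no clustering:

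Probability that the lower 95% limit exceeds zero = Φ{(q₁ − q₀)/√[(q₀(1−q₀) + q₁(1−q₁))/6,840] − 1.96}

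| Scenario | z before subtracting 1.96 | Detection |
|---|---|---|
| Severe 0.35% to 0.70% (5% of AEs, doubled) | 2.83 | 81% |
| Severe 0.14% to 0.28% (2% of AEs, doubled) | 1.79 | 43% |
| Severe 0.07% to 0.14% (1% of AEs, doubled) | 1.26 | 24% |
| Moderate-or-severe 2.1% to 3.15% | 3.84 | 97% |

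A simulation of 4,000 trials with between-gote variation agrees: for the 0.35% to 0.70% case it gives 91% non-inferiority and 81% detection. All the severe and moderate shares are assumptions.

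**The case against.** A reader might infer that the whole safety decision rests on the any-AE proportion, or that a rise in severe events would pass unseen. The documents do not support either reading. SAEs are named in the primary outcome (section 10). A severe AE is handled as a possible SAE, which prompts an immediate analysis and a DSMB call (section 8.5 and the charter). Severe AEs and SAEs receive a full investigation and their own analysis. The charter gives the DSMB a general duty to watch for differences between interventions, and under section 8.8 it reviews the final data before advising on the rest of the woreda. A marked shift would therefore reach the body that advises on wider use.

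Other objections also have force:
- The kebele line sits in a short descriptive list and does not exclude a split by arm. Under section 8.8, where adjacent gotes form each arm, kebeles might fall largely within one arm. Section 8.1 describes the allocation differently.
- Severity tables by arm are routine SAP content, and the SAP is not shown.
- Directly after the 31% figure, section 4.1 cites modelling that found the higher ivermectin levels well within safety ranges. The documents do not predict that intensity will rise while the count stays constant.
- The 91% follows by construction once the any-AE rates are set equal.

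These points limit the finding without removing it. Case-by-case review and a general DSMB remit specify no contrast of severe events between arms and do not alter the non-inferiority verdict. The protocol itself, not an unseen SAP, fixes the grade-blind rule, the covariate and the mild/moderate trigger.

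**Conclusion.** The point holds in a limited form. Both stated thresholds count AEs of any grade, and no section specifies a separate comparison of severe AEs between arms. A shift from mild to severe would leave the favourable verdict unchanged: about 91% probability of declaring non-inferiority with 36 gotes and 7% any-AE in both arms (86% to 95% over the variants shown), whatever the grade mix. This property of the rule does not depend on any assumed severe share. The case counts and detection probabilities do.

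It would go too far to say that the plan ignores severity, or that a favourable conclusion should be barred whenever a lower confidence limit for a severity difference exceeds zero. Such a bar would have no margin, although the plan accepts a 1.5-point rise in AEs. Across two checks it could raise a false alarm in up to about 5% of trials (2.5% each). This is a gap in the stated analysis that should be closed. It does not undermine the design.

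**What to change.** 1. In section 8.9, replace the kebele severity line with the proportion having at least one moderate-or-severe AE, and the proportion having at least one severe AE or SAE, by arm. Give the gote-adjusted risk difference and 95% interval for each.
2. Name these as key secondary safety estimates, reported beside the non-inferiority result and weighed before that result is called unequivocal. No automatic veto is proposed.
3. Remove severity as a covariate from the AE regression.
4. Reconcile the mild/moderate-only between-arm comparison in section 8.5 and the DSMB charter with the any-grade primary outcome. How the trigger should read is for the sponsor and the DSMB.

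The cost is protocol and SAP wording plus two estimates from data already collected. The sample size does not change. The drawback is low precision if severe events are rare, so an interval that includes zero should not be read as evidence of equal severity.
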